### Secondary outcomes

The secondary outcomes of the study will be healthcare utilization and guideline adherence. Healthcare utilization will be operationalized using hospital admission rates and hospital length of stay. Guideline adherence will be operationalized as scheduled primary care provider and specialist visits.

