### Evidence based recommendations

In order to minimize the burden of COPD, high quality guidelines have been developed [1–4]. These guidelines generally specify disease identification through spirometry, management through a combination of smoking cessation, vaccination, pharmacologic therapy and physical activity, and proper management of COPD exacerbations (aeCOPD) with pharmacologic therapy [11]. When implemented, these steps have shown substantial improvements in patient quality of life, as well as a reduction in healthcare utilization. These benefits have been demonstrated in the Saskatoon Health Region (SHR) where the application of best practices through the LiveWell COPD program resulted in a 65% reduction in hospital admissions, a 61% reduction in inpatient days and a 44% reduction in emergency room visits [12].

Although these results are promising, evidence suggests that the creation of guidelines is inadequate [13–15] as passive dissemination alone rarely results in changes in practice [3, 16, 17]. Estimates across the healthcare environment suggest that 30–40% of patients do not receive treatments with proven effectiveness [18].

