## Methods/design

### Aims of the CPWs

In order to improve knowledge translation and address the limited evidence on the effectiveness of CPWs we will implement and evaluate two CPWs for the treatment of COPD within the province of Saskatchewan. The first CPW will be implemented in a predominently urban health region (Regina Qu’Appelle; RQHR) and the second will be implemented in a rural health region (to be chosen following implementation in RQHR). The development and implementation of the CPW will utilize the following steps:Identify and current best practices for the diagnosis and management of COPD;Use idenfied best practices in combination with local resources in the development of two CPWs;Tailor evidence-informed implementation strategies to the local context with the goal of encouraging uptake of the developed CPWs;Implement and pilot test the COPD pathway in two different Saskatchewan health regions; one urban (RQHR) and one in a rural (to be chosen at a later date);Evaluate the effectiveness of the CPWs based on chosen outcomes;Improve on areas of weakness identified through the evaluation

These steps are described in detail through the remainder of the documents. By applying this process we hope to achieve the following goals:Increase quality of care;Reduce healthcare utilization;Increase guideline adherence

To determine if these goals are met, the project will utilize an interrupted time series (ITS) design with control groups. We will compare the health regions which implement CPWs to both the control groups and to pre-inteventions measures.

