### Design

We propose a quantitative health services research project using an interrupted time series (ITS) design in the form of a multiple baseline approach with control groups [37]. This methodology allows post-intervention trends to be compared with pre-intervention trends as well as the control group. We will compare the health regions which implement CPWs (intervention group) to both health regions which have not implemented the CPW (control group) and to pre-inteventions measures. Specificially, we will look at changes in:Quality of care, measured by:○ Hospital readmission rates;○ Unscheduled visits (emergency department);
Healthcare service utilization, measured by:○ Admissions rates;○ Length of stay;
Adherence, measured by:○ Scheduled visits (primary care providers, specialists)

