### Analysis

Analysis will be conducted using segmented regression analysis. This form of regression is used to control for pre-existing trends by estimating changes in intercept and slope after the introduction of the intervention. Both an immediate impact (change in intercept) and gradual changes over time (change in slope) can be detected [38]. This design is less susceptible to the common threats to internal validity that occur in most observational study designs, including maturation and regression to the mean.

We will report the β coefficients which measure the following variables: model intercept prior to implementation (β_0_), model slope prior to implementation (β_1_), model intercept following implementation (β_2_) and model slope following implementation (β_3_). In this analysis a statistically significant β_2_ coefficient which is smaller than β_0_ suggests a decrease in the rate following the intervention. Similarly, a statistically significant negative β_3_ coefficient suggests a decrease in the rate of interest.

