### Sample size considerations

We used two years of existing readmissions data to conduct power calculations for the ITS design. This was done using the simulation approach developed by Zhang et al. [39]. We estimated the Mean Squared Error (MSE), baseline intercept, and trend in the pre-intervention period using the pre-intervention data. Further we assumed either moderate or strong autocorrelation (AR(1) = 0.4 or 0.8); a change in intercept of 0, and two-sided α = 5%. We varied the number of post-intervention observation points from 6 to 30 and calculated the required change in slope that can be detected with at least 80% power. The analysis of the pre-intervention data showed strong secular trends in the primary outcome measure. We anticipate that for most outcomes, monthly observations will be used; in the case of small denominators for some outcomes, we may need to use quarterly or semi-annual intervals.

Based on these calculations we will use 36 pre- and post-intervention data points for most outcomes (with a minimum of 6 pre- and post-intervention data points for some secondary outcomes). As each data point for the primary outcome will contain one month’s data this equates to three years of pre-intervention and three years of post-intervention data.

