### Data sources

Data regarding hospital admissions rates, hospital readmission rate and length of stay will be retrieved through the Discharge Abstracts Database from the Canadian Institute of Health Information (CIHI) [40]. Data regarding scheduled GP visits will be retrieved through the Saskatchewan Health Quality Council Database. Data will be retrieved at the health region level and disaggregated to the hospital level.

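### Length of stay exists only for admissions that occur, so it can rise while total bed use falls; total inpatient days should be added as the utilization measure

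*Protocol article*

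**What the plan says.** One of the three goals under Aims of the CPWs is "Reduce healthcare utilization". Two sections fix how this is measured. Secondary outcomes states: "Healthcare utilization will be operationalized using hospital admission rates and hospital length of stay". Design lists the same pair: "Healthcare service utilization, measured by:○ Admissions rates;○ Length of stay". Neither section lists total inpatient days.

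Data sources gives the origin of both measures: "Data regarding hospital admissions rates, hospital readmission rate and length of stay will be retrieved through the Discharge Abstracts Database". Length of stay is therefore a property of a hospital stay that took place.

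The Analysis section specifies segmented regression and explains how its coefficients are read, for example "a statistically significant negative β_3_ coefficient suggests a decrease in the rate of interest". It does not discuss how two outcomes under one heading are to be read together.

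The Background, under Evidence based recommendations, reports that the LiveWell COPD programme in the Saskatoon Health Region "resulted in a 65% reduction in hospital admissions, a 61% reduction in inpatient days and a 44% reduction in emergency room visits". There the measure is total inpatient days, not length of stay.

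**The concern.** The pathway is meant to keep some patients out of hospital. Each admission it prevents lowers the admission rate and also drops out of the set of stays over which length of stay is calculated. Success on one utilization measure therefore changes who is counted in the other. If the prevented admissions tend to be the shorter ones, those that remain are longer on average, and mean stay goes up although no single stay has lengthened.

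The control regions do not remove this. The change in case mix would be caused by the pathway and would occur only where the pathway is in use, so it would appear as an intervention effect on length of stay.

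What is at stake is the answer on inpatient utilization. With admissions down and mean stay up, the two measures disagree in sign, and neither alone says whether bed use fell. The reverse can also happen: admitting more short-stay patients would shorten mean stay while bed use rose.

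**Working it through.** **Inputs.** Both come from Evidence based recommendations: admissions down 65%, and "a 61% reduction in inpatient days". The article gives no underlying counts, so these percentages cannot be re-derived. It states no length-of-stay effect for this programme, so there is no planned figure to reproduce first.

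**Identity.** Inpatient days = admissions × mean stay per admission. Hence the ratio for mean stay = (ratio for days) / (ratio for admissions).

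**Step 1. Implied mean stay.**
- Admissions ratio: 1 − 0.65 = 0.35
- Inpatient-days ratio: 1 − 0.61 = 0.39
- Mean-stay ratio: 0.39 / 0.35 = 1.114, a rise of about 11%
- Check: 0.35 × 1.114 = 0.39

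**Step 2. Rounding of the two percentages.**
- Lowest: (1 − 0.615) / (1 − 0.645) = 0.385 / 0.355 = 1.085
- Highest: (1 − 0.605) / (1 − 0.655) = 0.395 / 0.345 = 1.145

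The rise is not an artefact of rounding. This range does not cover sampling error, which the article gives no means of calculating.

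**Step 3. How much selection is needed.** If the remaining stays kept their baseline length, the prevented admissions would have averaged 0.61 / 0.65 = 0.94 of the baseline mean stay. A small difference is enough when many admissions are prevented. Two aggregate ratios cannot show whether selection or longer individual stays produced the rise.

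**Step 4. General form.** Let a fraction a of admissions be prevented, with mean stay r times the baseline mean, and let other stays be unchanged. Then:
- change in bed-days = −a·r
- mean-stay ratio = (1 − a·r) / (1 − a), which exceeds 1 whenever r is below 1

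For a = 0.20 (an assumption, not a figure from the article):

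| r | Bed-days | Mean stay |
|---|---|---|
| 0.50 (assumed) | −10% | 0.90/0.80 = 1.125 (+12.5%) |
| 0.75 (assumed) | −15% | 0.85/0.80 = 1.0625 (+6.25%) |
| 0.94 (from step 3) | −18.8% | 0.812/0.80 = 1.015 (+1.5%) |

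The direction depends only on r being below 1. The size depends strongly on both a and r, and at a modest effect with weak selection it is small.

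**The case against.** The strongest reply is that the plan does not rely on length of stay alone. The admission rate stands beside it in the same sentence and would show the 65% fall in the illustration. The two measures are the factors of bed use, so a careful reader could multiply them. This stands, and it limits the point to one component. It does not remove the point: two separately fitted regressions give no confidence interval or test for the change in their product, and the stated goal concerns utilization, not its factors.

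A reader might go further and infer that the plan would score a 61% fall in inpatient days as an 11% worsening. The article does not support that. The Analysis section describes the direction of coefficients and defines no success rule. It could not serve as one for every outcome, since fewer scheduled visits would not naturally mean better adherence. No section combines the two utilization measures into one verdict.

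Three further objections also stand. First, the 65% and 61% are cited background results, with patient set, period and design not shown. They come from the region that Settings names as the urban control, and they are not a planning effect. Second, the 11% needs length of stay to be a mean per admission. That is the ordinary reading, but the article does not spell it out, and a median could behave differently. Third, length of stay has its own justification: the section on clinical pathways cites reductions in it with COPD pathways, so dropping it as an analysed outcome would be a debatable trade-off. The remedy below therefore keeps it.

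**Conclusion.** The point holds in a limited form. Length of stay is defined only for admissions that occur, and the pathway aims to reduce admissions. Whenever the prevented admissions are shorter than average, mean stay per admission rises while total bed use falls, and the two named utilization measures give opposite signals.

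On the article's own background figures the implied mean stay is 1.11 times baseline (1.085 to 1.145 with rounding), alongside a 61% fall in inpatient days. This is an illustration only. It rests on mean stay per admission and on both percentages referring to the same patients and period.

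The point affects the length-of-stay component of a secondary outcome. Readmission and emergency department rates, the primary outcomes, are untouched. The change is nevertheless worth making, because a measure that answers the utilization question directly can be had from the same data.

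**What to change.** In Design and Secondary outcomes, add total COPD inpatient days per population per period as the measure of inpatient utilization, with a prevented admission counting as zero days. Use the same population denominator as for the admission rate, so that the three measures are arithmetically linked, and analyse the new outcome with the segmented regression already planned.

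Keep length of stay per admission as an analysed measure of in-hospital care. State that it is to be interpreted jointly with the admission rate and is not stand-alone evidence on utilization.

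The cost is a wording change in two sections and one derived variable. Inpatient days are the sum of stays already being retrieved from the Discharge Abstracts Database, so no new data are needed. The downside is one more secondary outcome, probably more variable from month to month than mean stay.

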### Analysis

Analysis will be conducted using segmented regression analysis. This form of regression is used to control for pre-existing trends by estimating changes in intercept and slope after the introduction of the intervention. Both an immediate impact (change in intercept) and gradual changes over time (change in slope) can be detected [38]. This design is less susceptible to the common threats to internal validity that occur in most observational study designs, including maturation and regression to the mean.

We will report the β coefficients which measure the following variables: model intercept prior to implementation (β_0_), model slope prior to implementation (β_1_), model intercept following implementation (β_2_) and model slope following implementation (β_3_). In this analysis a statistically significant β_2_ coefficient which is smaller than β_0_ suggests a decrease in the rate following the intervention. Similarly, a statistically significant negative β_3_ coefficient suggests a decrease in the rate of interest.

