### Settings

In order to evaluate the interventions, each health region will be matched with a control. For the intervention implemented in the Regina Qu’Appelle Health Region (RQHR), Saskatoon Health Region (SHR) will act as the control. Rural health regions will be chosen following implementation in RQHR and will occur following stakeholder consultation. As with the urban setting, the chosen rural health region will be compared to an appropriate control health region.

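### The design promises a comparison with matched control regions, but the stated coefficients and reading rules are all within one series and contain no intervention-versus-control contrast

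*Protocol article*

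**What the plan says.** The Abstract, Aims of the CPWs, Design and Settings all describe a controlled study. Design calls it an "interrupted time series (ITS) design in the form of a multiple baseline approach with control groups" and adds: "This methodology allows post-intervention trends to be compared with pre-intervention trends as well as the control group". It goes on: "We will compare the health regions which implement CPWs (intervention group) to both health regions which have not implemented the CPW (control group", with the regions' own earlier data as the second comparator. Settings states that "each health region will be matched with a control". RQHR is paired with SHR, and the rural pair is still to be chosen.

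Analysis is the only section that describes the model. It names segmented regression and lists the quantities to be reported: "model intercept prior to implementation (β_0_), model slope prior to implementation (β_1_), model intercept following implementation (β_2_) and model slope following implementation (β_3". It then gives two rules for reading them: "a statistically significant β_2_ coefficient which is smaller than β_0_ suggests a decrease in the rate following the intervention" and "a statistically significant negative β_3_ coefficient suggests a decrease in the rate of interest". The section does not mention the control regions.

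Sample size considerations says: "We used two years of existing readmissions data to conduct power calculations for the ITS design". Its listed inputs are the MSE, a baseline intercept and a trend estimated from pre-intervention data, AR(1) of 0.4 or 0.8, no change in intercept, two-sided 5%, at least 80% power for a change in slope, and 6 to 30 post-intervention points. It lists no control-series parameter and no between-region correlation, and it does not say which regions supplied the data.

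**The concern.** A control region is there to separate a pathway effect from anything else that changes at about the same time. Segmented regression on one series handles a trend that simply continues. It cannot handle a change in level or slope that happens in both regions near the implementation date. The Analysis section gives a rule for deciding that the rate has fallen, and no part of that rule looks at the control.

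Two things are at stake. The first is a false positive on the primary outcome, which matters because the Discussion plans to extend similar pathways across the province if they are found effective. The second is the power statement: if it was computed for one series, it concerns a different quantity from the comparison the design promises.

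**Working it through.** **1. The plan's own figure.** The 36 pre- and 36 post-intervention points cannot be reproduced. The MSE, intercept, trend and detectable slope change are not given, and 36 lies outside the simulated range of 6 to 30. Only the conversion checks: 36 / 12 = 3 years. The comparison below is therefore scale-free.

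**2. Terms named against terms needed.**

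| Needed for a controlled comparison | In the Analysis section? |
|---|---|
| Intercept and slope before | Yes, β0 and β1 |
| Intercept and slope after | Yes, β2 and β3 |
| Region difference in baseline level and trend | No |
| Difference in level change, intervention minus control | No |
| Difference in slope change, intervention minus control | No |
| Rule for using the control result | No |

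The opening of that section speaks of changes in intercept and slope, while the coefficient labels describe post-period values. I use the change in slope, as the power text does.

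**3. Shared change, no pathway effect.** With known AR(1), the slope change detectable with 80% power is k × SE, where k = 1.960 + 0.842 = 2.802. If both regions share a slope change of f × k × SE, the single-series test rejects with probability Φ(fk − 1.96) + Φ(−fk − 1.96):

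| f | Single-series rejection |
|---|---|
| 0.25 | 10.8% |
| 0.50 | 28.8% |
| 0.75 | 55.6% |
| 1.00 | 80.0% |

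The shared change cancels in the intervention-minus-control contrast, which stays at 5%.

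**4. Power for the controlled contrast.** Assume equal variance and the same AR(1) in both regions, with between-region error correlation ρ. The document does not give ρ, so it is varied. The variance of the difference in slope change is 2(1 − ρ) times the single-series variance, so the SE ratio is r = √(2(1 − ρ)). For an effect with 80% single-series power, power = Φ(2.802/r − 1.96):

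| ρ | r | Power |
|---|---|---|
| 0 | 1.414 | 50.8% |
| 0.25 | 1.225 | 62.8% |
| 0.50 | 1.000 | 80.0% |
| 0.75 | 0.707 | 97.7% |

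Generalised least squares gave the same ratios at 24+6, 24+18, 24+30, 36+18 and 36+36 points, with AR(1) 0.4 and 0.8.

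At 36+36 and ρ = 0, the detectable slope per month in error-SD units is 0.094 for a single series and 0.133 for the contrast (AR(1) 0.4), or 0.158 and 0.223 (AR(1) 0.8).

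**5. Simulation check.** In 20,000 simulated series (36+36, AR(1) 0.4, ρ = 0), single-series power was 79.3%, controlled power was 50.2%, and the controlled contrast rejected 5.0% of the time under a purely shared change.

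**The case against.** The best defence is that this is a journal article. It commits several times to comparing with controls, it writes out no equation, and it does not say that the four coefficients are the only terms. Interaction terms could sit in a fuller analysis plan. This stands against one tempting inference, that the control regions will never enter the effect estimate; the stated intent is otherwise. It does not rescue the Analysis section. That section goes beyond naming a method: it lists the coefficients and says what result counts as a decrease. A fuller plan that added the contrast would have to replace that rule.

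A second point is that the design is a multiple baseline. The rural region starts after RQHR, so an event near June 2017 would not coincide with the rural start. This is real but partial protection. It does nothing for the RQHR result taken alone, and the Analysis section gives no rule for using the stagger. It would nevertheless be too strong to say that any province-wide event would be credited to the pathway.

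Third, a reader might infer that the power calculation is definitely single-series and that true power is about 51%. The text supports neither. The single-series basis is inferred from the listed inputs, and 51% requires zero correlation between regions. Shared provincial influences would make the correlation positive, and above 0.5 the contrast gains power.

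Finally, a controlled contrast removes only what both regions share equally, and SHR already runs the LiveWell COPD programme. That limits how the contrast is interpreted; it is no reason to leave the contrast out.

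**Conclusion.** The concern holds in this form: the Analysis section's coefficients and reading rules do not carry the comparison that the design promises, and read as written they would take a shared change near implementation for a pathway effect. This is a stated rule in conflict with the design, not missing detail, and it concerns the primary effect estimate.

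The size depends on a shared change that the document cannot quantify. The false-positive rate runs from 10.8% to 80% for shared slope changes between one quarter and the whole of the single-series detectable change, against a nominal 5%.

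The power part is weaker. The calculation appears to address a different quantity. With equal variances and a common, known AR(1), controlled power ranges from about 51% to 98% over correlations from 0 to 0.75. Whether power falls or rises cannot be told from the document.

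**What to change.** For each matched pair, fit one segmented regression that allows for autocorrelation and for correlation between the two regions. With R = 1 for the intervention region, P = 1 after implementation and s = time since implementation (0 before):

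Y = γ0 + γ1·t + γ2·P + γ3·s + γ4·R + γ5·R·t + γ6·R·P + γ7·R·s + error.

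- Declare γ6 (difference in level change) and γ7 (difference in slope change), intervention minus control, as the effect estimates.
- Define every coefficient explicitly as a change or as a post-period value. New symbols avoid confusion with the article's β2 and β3, which are labelled as post-period values.
- Report the single-series results as supportive.
- State which regions and how many series the existing power calculation used. Re-run the simulation for γ7 and give the detectable difference over a range of between-region correlations.
- Note in the interpretation that SHR already has a COPD programme in place.

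Settle this before outcome data are analysed, so that the choice between single-series and controlled estimates cannot follow the results. The cost is revised wording, a little more analysis work and a re-run simulation on control data already planned. The stated detectable effect may turn out less favourable.

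### The coefficient definitions conflict with the stated change model, and the rule comparing β2 with β0 is invalid under either coding

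*Protocol article*

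**What the plan says.** The Analysis section opens by saying that the method is used to "control for pre-existing trends by estimating changes in intercept and slope after the introduction of the intervention", and names an immediate effect as a change in intercept and a gradual effect as a change in slope.

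The next paragraph lists what will be reported. β0 and β1 are the intercept and slope before implementation. The other two are "model intercept following implementation (β_2_) and model slope following implementation (β_3"). As printed, these are post-period values and not changes.

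Two interpretation rules follow:

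- Level: "a statistically significant β_2_ coefficient which is smaller than β_0_ suggests a decrease in the rate following the intervention".
- Slope: "a statistically significant negative β_3_ coefficient suggests a decrease in the rate of interest".

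Sample size considerations returns to changes. The simulation assumed "AR(1) = 0.4 or 0.8); a change in intercept of 0, and two-sided α = 5"%, and the authors "calculated the required change in slope that can be detected with at least 80% power". The same section reports: "The analysis of the pre-intervention data showed strong secular trends in the primary outcome measure". It gives neither the direction nor the size of that trend.

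**The concern.** An interrupted time series estimates an intervention effect by comparing the post-period with the continuation of the pre-period trend. As printed, neither rule makes that comparison. The level rule sets two intercepts side by side without testing their difference. The slope rule looks at the sign of the post-period slope without reference to β1.

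These are the only rules that the article gives for reading its coefficients, and readmission and emergency department rates, the two primary outcomes, would be read through them. Where the outcome already has a strong trend, as the authors report, a rule that ignores the trend can credit the pathway with a decline that was already under way, or miss a real reduction against a rising background. If the software returns change coefficients, the printed level rule can present a significant worsening as an improvement.

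**Working it through.** The article states no error rate for these rules. It also gives no mean squared error, baseline or detectable slope, so there is no figure of its own to reproduce. The check is logical first, then a simulation on assumed inputs.

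**Step 1. Printed definition.** Before: Y = β0 + β1·t. After: Y = β2 + β3·t′. The text does not say where t′ starts, so two placements are considered: (A) at the start of the post segment, (B) at month 0 of the whole series.

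Suppose there is no intervention effect and the prior slope is s per month.

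- β2 against zero: a readmission or emergency department rate is well above zero, so β2 is always significant. The rule reduces to whether the estimate of β2 is below the estimate of β0.
- Under A, with 36 pre-intervention months, the expected β2 − β0 is 36·s. At s = −0.05 SD per month this is 36 × (−0.05) = −1.8 SD, with no effect at all.
- Under B, the expected β2 − β0 is 0, so the rule is a coin toss.
- Under both, the expected β3 is s, which equals β1. A significant negative β3 then says only that the earlier decline continued.

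**Step 2. Change definition.** Y = β0 + β1·t + β2·post + β3·(time since implementation)·post. Here β2 is a difference and β0 a level, so β2 < β0 holds for every reduction and for every increase smaller than the baseline. With a baseline of 20, a significant change of +3 satisfies 3 < 20 and would be read as a decrease. The β3 rule is correct under this coding.

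**Step 3. Size under the printed definition.** From the article: 36 pre and 36 post points, AR(1) of 0.4 or 0.8, two-sided α of 5%. Assumed: a baseline 20 SD above zero, prior slopes from −0.10 to +0.05 SD per month, no intervention effect, generalised least squares with known autocorrelation, 4,000 series per setting. Ranges span the two autocorrelations.

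| Assumed prior slope (SD/month) | Decrease called by either rule, placement A | Placement B |
|---|---|---|
| 0 | 51–53% | 51–53% |
| −0.01 | 67–75% | 54–56% |
| −0.02 | 79–91% | 57–63% |
| −0.05 | 99–100% | 79–97% |
| −0.10 | 100% | about 100% |

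In flat series the β2 rule alone gives 49–51% and the β3 rule alone 2–3%. In falling series the β3 rule alone gives 31–57% at −0.05 and 84–99% at −0.10.

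The Discussion section of the article ends data collection 18 months after the start of implementation. With 18 post points and a slope of −0.05, the either-rule figures are 96–100% (A) and 60–62% (B).

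A rising trend works the other way under A. At +0.05 SD per month the expected β2 − β0 is 36 × 0.05 = +1.8 SD, so a real step down of less than 1.8 SD still leaves the expected β2 above β0. With 18 post points and no effect, either rule then calls a decrease in 1.6% (AR 0.4) or 7.2% (AR 0.8) of series. Under B the β2 rule stays near 50%.

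**Step 4. Size under the change definition, 36 + 36 points.** The printed β2 rule fires in 4.5–5.8% of null series whatever the trend; about half of these (2.3–3.0% of series) are significant increases labelled as decreases. A true upward step of 3 SD at AR 0.4 is labelled a decrease in 99.5% of series. The β3 rule gives 2.1–3.0%.

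**Step 5. After correction.** With change coding, and a decrease called only when the change itself is negative and significant, false decreases are 2.1–2.8% for level and 2.1–3.0% for slope, whatever the prior slope. Calling a decrease on either one gives 4.3–5.4%.

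**The case against.** The best defence is that the coefficient list is mislabelled and the authors intend the standard change model. The opening of the Analysis section and the power calculation both speak of changes, so this is plausible. It rescues the β3 rule completely. It does not rescue the β2 rule, because comparing a change in level with a baseline level has no meaning.

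A reader might infer that the analysis would declare a decrease in about half of all null series and in nearly all series that were already falling. The documents do not support that as a general statement. The first figure needs the printed definition and comes from the β2 rule: it applies to flat series, or to any prior trend when both intercepts sit at month 0. The second needs the printed definition, the post intercept at the start of its own segment, and a decline of roughly 0.05 SD per month or more; weaker declines gave about 54–91%. Baseline, SD and slope are all assumed. The reported strong secular trends could be rising. Under change coding neither rate occurs.

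It is also fair to say that the article calls these patterns suggestive and does not make them a formal success criterion, and that it commits separately to a comparison with control regions. Both points stand. They reduce the weight that the rule carries, but the printed guidance on reading the primary outcomes remains incorrect.

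**Conclusion.** The point holds and the text is wrong as written. Two parts need no assumption about trend, variance or autocorrelation: the coefficient definitions contradict the change model described in the same section and in Sample size considerations, and the comparison of β2 with β0 is invalid under either coding. The criticism of β3 is conditional on the printed definition as a post-period slope.

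The size is illustrative only. Under the printed definition and no effect, the β2 rule calls a decrease in about 50% of flat series, and either rule does so in roughly 54% to 100% of falling series, depending on slope, autocorrelation and where the intercept is placed. A rising trend would instead tend to hide real decreases when the intercept is placed at the start of the post segment. Under change coding the harm is different: the β2 rule can report a significant increase as a decrease.

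**What to change.** Rewrite the second paragraph of the Analysis section:

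- Define Y_t = β0 + β1·time + β2·post + β3·(time since implementation)·post, with β2 the change in level from the projected pre-intervention trend and β3 the change in slope from β1.
- Test β2 and β3 each against zero, with a 95% confidence interval. Delete the comparison of β2 with β0.
- Report the two changes together. Do not declare improvement when either one is significant: that roughly doubles the one-sided false-decrease rate (4.3–5.4% against a nominal 2.5%) and could call improvement when the level falls but the slope worsens. Alternatively, name the change in slope as the main test, since the power calculation rests on it.
- Use the corresponding group interaction terms for the comparison with control regions.
- State the favourable direction for each outcome: a decrease for readmission and emergency department rates, but not for scheduled visits, which the article uses to measure adherence.

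The cost is one paragraph of text. No data collection, sample size or patient procedure changes.
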